**Methods/Design:**

This is a mixed (retrospective and prospective) longitudinal observational study enrolling 90 patients who will be recruited from a reference center for CD in Brazil. Patients with CCC receiving AMIO will be compared with those not receiving the drug. AMIO was prescribed at the discretion of the treating physician, independently of the present study. Eligible participants will be invited to participate during routine medical appointments. Clinical data, including electrocardiographic and echocardiographic parameters obtained during routine follow-up, will be retrospectively extracted from medical records. Blood samples will be collected at predetermined time points. The primary endpoint will be the inflammatory profile and serological reactivity to anti-*T. cruzi* in CCC patients. Secondary endpoints will include: (**1**) cardiovascular events; (**2**) CCC progression; (**3**) implantable cardioverter-defibrillator (ICD) implantation; (**4**) heart transplantation; (**5**) all-cause death and (**6**) a composite endpoint. The association between AMIO use and longitudinal changes in continuous variables will be determined using mixed linear models. Cox regression analysis will be used to investigate the relationship between AMIO use and selected outcomes (cardiovascular events, CCC progression, and death), adjusted for potential confounders. Hazard ratios (HRs) with 95% confidence intervals (CIs) will be reported.

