### Study design

This is a mixed (retrospective and prospective) longitudinal observational study designed to evaluate the association between chronic use of amiodarone (AMIO) and the following:

(I)**Primary outcome:** inflammatory profile, serologic reactivity to anti-*T. cruzi* antibody, and parasitic load;(II)**Secondary outcomes:** cardiovascular events (new sustained atrial arrhythmias, new sustained or non-sustained ventricular tachyarrhythmias, stroke, heart failure, atrioventricular block, and cardiovascular hospital admissions), CCC progression, internal cardioverter-defibrillator (ICD) implantation, heart transplantation, all-cause death, and a composite endpoint (including the aforementioned cardiovascular events, disease progression, ICD implantation, heart transplantation, and death).

Patients with CCC who take AMIO (exposed group) will be compared with those who do not take this drug (non-exposed group). To minimize potential confounding, patients will be matched based on the stage of CCC according to the Brazilian Consensus on Chagas Disease (A and B1 *versus* B2 and C), age (<50 years *versus* >50 years), and sex (female *versus* male) [15].

Clinical and laboratory data including blood tests, ECG, transthoracic two-dimensional echocardiography (ECHO), and 24-hour Holter monitoring, will be evaluated at three different time points:

(i)**Retrospective data**: from up to 3 years before the start of the study;(ii)**Baseline/recruitment**: at the time of inclusion in the study;(iii)**Prospective data**: during the 2 years of follow-up after recruitment;

The duration of the study, totaling five years of clinical follow-up, was established considering the CCC progresses at a rate of approximately 2% per year [22]. At recruitment, blood samples will be collected for biochemical and molecular analyses to obtain information related to the study’s primary outcome (Table 1) (Fig 1).

**Table 1 pone.0347305.t001:** AMIO-CHAGAS’s study Chronogram: Enrollment, Interventions and Outcome Assessments.

			Retrospective data	Recruitment	Prospective data
			2020 −2022	2023 - 2025	2025 - 2027
**Primary outcome:**	**Immunomodulatory effect**	Gene expression of CCC progression biomarkers in PBMCs	**–**	**x**	**–**
		Determination of serum levels of cytokines and nitric oxide	**–**	**x**	**–**
	**Trypanocidal effect**	Determination of anti-*T. cruzi* antibody titers	**–**	**x**	**–**
		*T. cruzi*-antigen quantification	**–**	**x**	**–**

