### Study population

Participant recruitment began on March 7, 2023, and is expected to be completed by December 2025. Participants are being recruited sequentially during their routine medical visits. Patients using AMIO are identified from the database of individuals monitored by the Clinical Research Laboratory on Chagas Disease at INI-Fiocruz. Only patients who have been receiving AMIO for at least three months will be included, ensuring adequate tissue impregnation with a cumulative dose of 10 g [23].

Inclusion criteria are as follows:

Confirmed diagnosis of CD, based on two serological tests with different methodologies (enzyme-linked immunosorbent assay [ELISA] and chemiluminescence) [14,15];Individuals over 18 years of age;Patients classified within the following CCC stages: A, B1, B2, and C [15].

Exclusion criteria are as follows:

Co-infection (HIV, hepatitis B and C, HTLV, Hansen’s disease, leishmaniasis and paracoccidioidomycosis);Immunosuppression of any nature;Cancer;Patients with stage D of CCC will be excluded due to their complex clinical management, including frequent hospitalizations and medication adjustments, which could affect the study’s feasibility.

Patients meeting the inclusion criteria will be invited to participate in the study, and written informed consent will be obtained from all individuals who agree to enroll.

Importantly, AMIO use was prescribed at medical discretion to treat atrial or ventricular arrhythmias [12], independently of this study, characterizing an observational study design.

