### Statistical analysis

Descriptive statistics were used to summarize the characteristics of the study population. Continuous variables will be presented as medians and interquartile ranges (IQR), and categorical variables as absolute and relative frequencies. Missing data will be assessed for their pattern and mechanism (i.e., missing completely at random (MCAR), missing at random (MAR), or missing not at random (MNAR)). The primary approach to handling missing data will be determined once the dataset is available. Depending on the extent and nature of missingness, appropriate strategies may include multiple imputation, complete case analysis, or sensitivity analyses to evaluate the robustness of the findings. The Shapiro-Wilk test will be used to assess the normality of continuous variables. When distributions deviate from normality, appropriate transformations or non-parametric tests will be applied.

Comparisons of patient characteristics according to AMIO use will be evaluated using the independent Student’s t-test for normally distributed continuous variables or the Mann-Whitney U-test for non-normally distributed data. Categorical variables will be compared using the chi-square test or Fisher’s exact test, as appropriate. Correlations between continuous variables related to the primary outcome will be assessed using Pearson or Spearman correlation coefficients, depending on data distribution. AMIO use and longitudinal changes in continuous variables will be analyzed using mixed linear models, adjusted for the duration of amiodarone use. Analyses of time course outcomes (e.g., cardiovascular events, disease progression, all-cause mortality) will be conducted using Cox proportional hazards regression models adjusted for potential confounders such as age, sex, comorbidities and previous etiologic treatment. Hazard ratios (HRs) and their 95% confidence intervals (CI) will be reported. A two-sided p-value ≤ 0.05 will be considered statistically significant.

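### The non-exposed group has no condition on past amiodarone use, so former users count as controls and their on-drug events are credited to the wrong group

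*Protocol article*

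**What the plan says.** The groups are defined in three places, each time by whether the patient takes the drug and without reference to past use. Study design has "Patients with CCC who take AMIO (exposed group) will be compared with those who do not take this drug (non-exposed group". The abstract has "Patients with CCC receiving AMIO will be compared with those not receiving the drug". Sample size splits the 90 participants into 45 who use amiodarone and 45 who do not.

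The exposed side has an entry threshold under Study population, justified by tissue impregnation: "Only patients who have been receiving AMIO for at least three months will be included". No matching condition is placed on the non-exposed side. The exclusion criteria cover co-infection, immunosuppression, cancer and stage D disease. Past amiodarone is not among them, and the article gives no look-back or washout.

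Clinical data reach back in time: "from up to 3 years before the start of the study", shown in Table 1 as 2020–2022. Follow-up then runs "during the 2 years of follow-up after recruitment". Under Statistical analysis, longitudinal changes are to be "analyzed using mixed linear models, adjusted for the duration of amiodarone use". The Cox models name age, sex, comorbidities and previous etiologic treatment as examples of confounders. They do not mention past amiodarone and do not describe exposure as varying over time.

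**The concern.** A patient who took amiodarone for years and stopped shortly before recruitment meets the wording of the non-exposed group. Two things follow.

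First, Table 1 collects cardiovascular events and disease progression retrospectively. Events that such a patient had while on the drug would be counted against the non-exposed group.

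Second, every primary marker is measured once, at recruitment. There is no value from before amiodarone, so the primary result rests wholly on the between-group contrast. If any effect outlasts treatment, former users among the controls shrink that contrast.

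Former users are plausible at this centre. The Background lists pulmonary, hepatic and thyroid toxicity among the drug's adverse effects, and the Discussion says its adverse effects limit its use. Patients who stopped for such reasons are also a selected group, which could move the event comparison in either direction.

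**Working it through.** **Step 1: who is non-exposed under the text.** Take three patients at recruitment.
- On amiodarone for three months or more: exposed.
- On amiodarone for less than three months: a taker, so not non-exposed, and kept out of the exposed group by the three-month rule.
- Used amiodarone in 2020–2022 and stopped before recruitment: does not take the drug, meets no exclusion, so non-exposed.

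Only the third is misclassified.

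**Step 2: which outcomes are touched (Table 1).** Marked as retrospective: cardiovascular events and disease progression. Prospective only: ICD implantation, transplantation, death and the composite. Recruitment only: all primary markers. Misattributed past events therefore affect two secondary outcomes. The primary markers are affected only through carry-over.

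**Step 3: the same problem in the exposed group.** Recruitment began on 7 March 2023. A patient enrolled that day with exactly three months of use started in early December 2022, so nearly all of 2020–2022 was off the drug. A similar patient enrolled later was off the drug for the whole of that window. A rule about controls alone does not correct this.

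**Step 4: the plan's own figure.** Inputs from Sample size: IFN-γ 43.75 ± 24.83 treated and 84.37 ± 35.08 untreated; TNF-α 27.08 ± 13.81 and 52.08 ± 23.38; two-sided 5%, power 80%. With SD = √[(s₁² + s₂²)/2] and n per group = 2(1.96 + 0.84)²·SD²/Δ²:
- IFN-γ: Δ = 40.62, SD = 30.39, n = 9 per group.
- TNF-α: Δ = 25.00, SD = 19.20, n = 10 per group.

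The larger gives 20 in total and 25 after dividing by 0.8. The stated 90 is not reproduced. That is a separate matter; here it means only that these inputs leave much spare power.

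**Step 5: dilution, as an illustration.** Let f be the share of controls who are former users and r the fraction of the effect they keep. Both are assumptions. The observed difference is Δ(1 − f·r).
- f = 10%, r = 50%: 40.62 × 0.95 = 38.6
- f = 10%, r = 100%: 40.62 × 0.90 = 36.6
- f = 30%, r = 100%: 40.62 × 0.70 = 28.4

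**Step 6: power on the plan's inputs.** Take the worst case, r = 100%. The control variance is then (1 − f)s₂² + f·s₁² + f(1 − f)Δ², where s₁ is the treated and s₂ the untreated SD. Use 36 per group (45 × 0.8, after losses) and power = Φ(Δ_obs/(SD·√(2/n)) − 1.96).

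| f | IFN-γ difference | Power | TNF-α difference | Power |
|---|---|---|---|---|
| 0 | 40.62 | 99.99% | 25.0 | 99.98% |
| 10% | 36.56 | 99.88% | 22.5 | 99.84% |
| 20% | 32.50 | 99.21% | 20.0 | 99.12% |
| 30% | 28.43 | 96.75% | 17.5 | 96.74% |
| 40% | 24.37 | 90.52% | 15.0 | 90.95% |
| 50% | 20.31 | 78.75% | 12.5 | 80.06% |

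For IFN-γ at f = 30%: control variance = 0.7 × 1230.6 + 0.3 × 616.5 + 0.21 × 1650.0 = 1392.9; SD = √[(616.5 + 1392.9)/2] = 31.7; power = Φ(28.43/(31.7 × 0.2357) − 1.96) = Φ(1.85), about 97%. The estimate is 30% too small while the test remains well powered.

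**The case against.** The group definition is one sentence, nowhere does the article say that former users will be enrolled as controls, and a fuller protocol may hold a look-back rule. It is true that the enrolment of former users follows from the wording and is not announced. But the article sets out exposure, inclusion and exclusion explicitly, and these fix the study's contrast. Applied as written, they admit former users.

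The duration adjustment might absorb past use. It is stated only for the mixed models of longitudinal change, and how a control's past use is coded is not said. It does not reach markers measured once, and it is not named for the Cox models.

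Restricting controls to never-users has its own cost. Amiodarone is prescribed here for arrhythmia, so former users are controls who once had the indication, and dropping them may worsen confounding by indication. This stands, and is why former users should be kept and reported.

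Three stronger readings are tempting, and the documents do not support them.
- A reader might infer that the protocol itself claims a lasting effect after stopping. It does not: tissue impregnation appears only as an entry threshold for users.
- A reader might infer that the study loses its power. For an effect of 0.67 SD with 37 per group and constant SD, 30% fully carried-over former users would cut power from 82% to 52%. No effect of that size appears in the protocol; on its own inputs power stays near 97%.
- A reader might infer that recent starters can also serve as controls. The wording already rules that out.

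**Conclusion.** The point holds as a badly fixed exposure definition. Applied as written, former users are non-exposed, and any cardiovascular events and progression they had on amiodarone in 2020–2022 are credited to the non-exposed group. That part needs no assumption about carry-over, only that some former users are enrolled.

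The effect on the primary markers is conditional. It requires that amiodarone affects the markers and that some of the effect persists after stopping; the bias is then towards no effect. With an assumed 10% to 30% of former users and 50% to 100% persistence, the contrast shrinks by 5% to 30%. The documents anchor neither range, so the true size is unknown. On the plan's own inputs the consequence is a biased estimate more than lost power. For events the direction is not determined.

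**What to change.** - Record amiodarone start and stop dates for every participant from the medical records. Amiodarone history is not in the listed variables under Data collection, but the planned duration adjustment already needs it.
- In the primary analysis, compare current users of at least three months with patients who have no recorded amiodarone use in the retrospective window or earlier.
- Report former users as a separate group, and add a sensitivity analysis that includes them as controls.
- For retrospective and prospective events, assign person-time by actual amiodarone status, as a time-varying exposure in the Cox models, in both groups. This also corrects the time before initiation in the exposed group.

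Make this an analysis-set rule and not an eligibility rule, since recruitment began in March 2023 and was due to finish by December 2025.

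The cost is a check of records and a few sentences of analysis text. Some enrolled controls leave the primary contrast: at the assumed 10% to 30%, about 5 to 14 of 45 (4.5 to 13.5), which also disturbs the matching on stage, age and sex. Never-users may differ in indication, which the sensitivity analysis addresses.

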**Secondary outcomes**:	Cardiovascular events	New sustained atrial arrhythmias and new sustained or non-sustained ventricular tachyarrhythmias, stroke, heart failure, atrioventricular block and cardiovascular hospital admissions	**x**	**–**	**x**
	Disease progression	Monitored by echocardiography (ECHO), electrocardiogram (ECG), 24-hour Holter	**x**	**x**	**x**
	ICD implantation	According to the medical prescription	**–**	**–**	**x**
	Heart transplantation	According to the medical prescription	**–**	**–**	**x**
	Death of all-cause	–	**–**	**–**	**x**
	Composite endpoint	–	**–**	**–**	**x**

CCC: Chronic Chagas cardiomyopathy; ECG: Electrocardiogram; ECHO: Echocardiography; ICD: Implantable cardioverter-defibrillator; PBMCs: Peripheral blood mononuclear cells.

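### Table 1 dates prospective event capture 2025–2027, which does not fit two years of follow-up for patients recruited from March 2023; separately, the look-back is tied to study start and leaves late recruits unobserved before baseline

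*Protocol article*

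**What the plan says.** The Study design section names three time points. Retrospective data come "from up to 3 years before the start of the study". Baseline is "at the time of inclusion in the study". Prospective data are gathered "during the 2 years of follow-up after recruitment". The same section describes the study duration as "totaling five years of clinical follow-up".

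The Study population section states: "Participant recruitment began on March 7, 2023, and is expected to be completed by December 2025". Recruitment is sequential, at routine visits.

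Table 1 gives the three columns calendar dates: retrospective 2020–2022, recruitment 2023–2025, prospective 2025–2027. The secondary outcome rows are marked as follows:

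| Row | 2020–2022 | 2023–2025 | 2025–2027 |
|---|---|---|---|
| Cardiovascular events | x | – | x |
| Disease progression | x | x | x |
| ICD implantation | – | – | x |
| Heart transplantation | – | – | x |
| All-cause death | – | – | x |
| Composite | – | – | x |

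The Statistical analysis section assigns cardiovascular events, progression and death to Cox models.

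**The concern.** If baseline is each patient's inclusion date and follow-up is the two years after it, follow-up for the cohort runs from March 2023 to December 2027. Table 1 starts it in 2025. Someone who used Table 1 as the capture schedule would not record a death or ICD implantation in 2024 in a patient enrolled in 2023.

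The Cox analyses depend on this. If time runs from inclusion but events count only from 2025, early recruits contribute time at risk in which no event can be seen. If risk time starts in 2025 instead, early recruits enter only if they are still alive, and their early events are lost. The number of affected patients depends on when they were recruited, so the loss is uneven across the cohort.

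The look-back raises a second and separate matter. It is fixed to the start of the study while baseline moves with the patient, so the retrospective data and the baseline measurements drift apart as recruitment proceeds.

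**Working it through.** **The plan's own figure.** In the text, 3 years of look-back + 2 years of follow-up = 5 years, as stated. Table 1 can also give 5: 2020–2022 is 3 years and 2026–2027 is 2 years, but with 2023–2025 (3 years) between them. If the prospective column starts in January 2025, the total is 3 + 3 = 6 years with a 2-year hole.

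**Inputs.** From the documents: recruitment from 7 March 2023 to December 2025, 2 years of follow-up, and the Table 1 column years. Assumptions: even accrual up to 31 December 2025; a prospective column that ends in December 2027; and a start month for that column, which Table 1 does not give (January 2025, July 2025 and January 2026 are tried). Time is in years from 7 March 2023, so accrual lasts 2.82 years.

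**The first recruit.** Two years end in March 2025. A January 2025 start captures 0.18 years and misses 1.82. A July 2025 or January 2026 start captures nothing. A patient recruited at the end of December 2025 loses nothing.

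**Average over the cohort, literal reading.** A patient recruited at time r, with the column starting at time s, misses min(2, max(0, s − r)) years. Averaged over r from 0 to 2.82:

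- January 2025, s = 1.82: (1.82²/2)/2.82 = 0.59 years; 0.59/2 = 29%.
- July 2025, s = 2.32: (2 × 0.32 + 2)/2.82 = 0.94 years; 0.94/2 = 47%.
- January 2026, s = 2.82: (2 × 0.82 + 2)/2.82 = 1.29 years; 1.29/2 = 65%.

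With 90 patients and 90 × 2 = 180 planned person-years, the two ends of the range are about 90 × 0.59 = 53 and 90 × 1.29 = 116 person-years. These apply to cardiovascular events, ICD implantation, transplantation, death and the composite. They do not apply to disease progression, which has an x in every column.

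**Non-literal reading.** If the dash describes only the inclusion visit and events are collected from inclusion anyway, the loss is 0%. The column date is then wrong, because follow-up would run from March 2023 and not from 2025.

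**Gap before baseline.** Counted from the end of 2022 to inclusion:

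| Recruited | Gap (years) | Part of the patient's own preceding 3 years inside 2020–2022 |
|---|---|---|
| 7 March 2023 | 0.18 | 2.82 |
| 1 January 2024 | 1.0 | 2.0 |
| 1 January 2025 | 2.0 | 1.0 |
| 31 December 2025 | 3.0 | 0 |

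**After anchoring on the recruitment date.** Every patient has 2.0 years captured after inclusion and no gap before it, so 3 + 2 = 5 contiguous years. Look-back spans March 2020 to December 2025 and follow-up March 2023 to December 2027.

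**The case against.** The strongest reply is that Table 1 is a chart of study phases. Its recruitment column holds the one-off blood assays, and incident death or transplantation cannot be assessed at an inclusion visit, so a dash is the natural entry there. The year 2025 stands in two columns, which suggests they are not exclusive calendar bins. On that view the text governs and no person-time is lost. This is a fair reading, and the document does not exclude it, so the 29% to 65% cannot be presented as an established loss. It still leaves the 2025–2027 label wrong for patients recruited in 2023 and 2024.

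One might also take the two years to begin when recruitment closes as a whole. That rescues the label, but the uncounted interval after inclusion then becomes real, up to 2.82 years for the first recruit.

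Four stronger inferences are tempting and are not supported:

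- That nothing is captured in 2023–2025. Disease progression is, "Monitored by echocardiography (ECHO), electrocardiogram (ECG), 24-hour Holter", and those examinations are annual.
- That text and table disagree on the look-back. Both refer to the start of the study, and 2020–2022 agrees with a start in March 2023. The gap is a weakness of the rule as stated, not a contradiction.
- That a prospective-only composite is an error because two of its components are also recorded retrospectively. The composite contains death, and everyone enrolled survived the look-back, so it can only be prospective.
- That the Cox analysis will ignore early events. The article does not state the time origin, and an analysis plan may do so.

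The primary outcome is measured once, at recruitment, and is not affected.

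**Conclusion.** The point holds as two limited findings.

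First, the prospective dates and the dashes in Table 1 cannot be reconciled with two years of follow-up after recruitment for patients enrolled from March 2023. The consequence lies between 0% (the dash refers to the inclusion visit and only the label is wrong) and 29% to 65% of planned post-enrolment person-time without capture of five of the six secondary outcomes. The upper range rests on a literal reading of the table, even accrual and an assumed start month between January 2025 and January 2026.

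Second, the look-back rule leaves late recruits up to about 3 years unobserved before baseline, and the stated five years are not contiguous for most patients. This does not depend on how the dash is read, but it does rest on the look-back closing at the end of 2022, as Table 1 dates it.

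It is more than a clerical slip, because Table 1 is the article's only schedule of outcome capture and the Cox analyses need to know when each patient's event capture begins. It should be corrected.

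**What to change.** Define both windows from each patient's recruitment date: look-back months -36 to 0, baseline at 0, follow-up months 0 to 24. Relabel the Table 1 columns in these terms; if calendar years are kept, follow-up should read March 2023 to December 2027. State that all events, including death, ICD implantation and transplantation, are captured from inclusion onward, and that the Cox time origin is inclusion. Keep the composite prospective, and say that cardiovascular events and progression contribute to it only over that same post-recruitment window; their retrospective counts can be reported separately.

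The cost is a correction of text and table, plus extraction of 2023–2025 events, and of the matching look-back data for later recruits, from the medical records already in use. No additional visits or blood samples are needed.

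### Table 1 and the five-year follow-up treat look-back cardiovascular events and CCC progression as outcomes while AMIO status is fixed at recruitment, so time and events before the first dose can count as exposed

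*Protocol article*

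**What the plan says.** - **Windows.** The Study design section lists retrospective data "from up to 3 years before the start of the study" and prospective data "during the 2 years of follow-up after recruitment". It then says: "The duration of the study, totaling five years of clinical follow-up, was established considering the CCC progresses at a rate of approximately 2% per year".
- **Outcome cells.** Table 1 defines the cardiovascular-event outcome as "New sustained atrial arrhythmias and new sustained or non-sustained ventricular tachyarrhythmias, stroke, heart failure, atrioventricular block and cardiovascular hospital admissions" and marks it in the retrospective and prospective columns. Disease progression is marked in all three columns. ICD implantation, heart transplantation, death and the composite are marked in the prospective column only.
- **Exposure.** Two fixed groups are compared: patients who take AMIO and patients who do not. Under Study population: "Only patients who have been receiving AMIO for at least three months will be included".
- **Indication.** The same section says that "AMIO use was prescribed at medical discretion to treat atrial or ventricular arrhythmias".
- **Model.** Under Statistical analysis: "Analyses of time course outcomes (e.g., cardiovascular events, disease progression, all-cause mortality) will be conducted using Cox proportional hazards regression models". The named adjustment factors are age, sex, comorbidities and previous etiologic treatment. Duration of AMIO use is named only for the mixed linear models. Matching is on stage, age and sex.

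**The concern.** The retrospective years are described as follow-up, and two event outcomes are marked in them, yet the exposed group is defined by something known only at recruitment. Three consequences follow if the look-back is analysed as written.

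1. A patient who started AMIO inside the window contributes unexposed time to the exposed group.
2. AMIO is started because of an atrial or ventricular arrhythmia. If that arrhythmia meets the outcome definition and falls in the window, it is counted as an event on AMIO although it preceded the drug and caused the prescription. Non-users have no matching built-in event.
3. Everyone must be alive and not in stage D at recruitment. Progression in the look-back that ended in death or stage D cannot be observed, so look-back progression is selected. The direction of that distortion is not certain.

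Age, sex, comorbidities and earlier treatment do not correct an event placed before exposure. At stake is the reading of the cardiovascular-event hazard ratio, which could show harm from AMIO where there is none.

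**Working it through.** **Step 1. The plan's own figure.** 3 retrospective + 2 prospective = 5 years. The stated windows reach five in no other way, so 3/5 = 60% of the counted follow-up lies before the prospective period. The same sentence ties this length to the 2% per year progression rate, so the look-back is treated as time in which outcomes accrue.

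**Step 2. How much look-back time can precede AMIO.** If the window ended at recruitment, a patient at the three-month minimum would have (36 − 3)/36 = 92% of it before the first dose. The text, however, places the window before the start of the study, and Table 1 gives 2020–2022 with recruitment in 2023–2025. On that calendar, a patient who started after 2022 has the whole look-back unexposed, and one who started before 2020 has none of it unexposed. The share therefore runs from 0 to 100% by patient, and the distribution is not given.

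**Step 3. Size of the arrhythmia bias when AMIO has no effect.** Assumptions, none of them in the documents: constant background rate λ of 5% or 10% per year in both groups; a five-year clock starting 3 years before recruitment; a share f of users with a qualifying prompting arrhythmia spread evenly over the first 2.75 years.

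Hand check. At 5 years the cumulative hazard is 5λ in non-users and 5λ − ln(1 − f) in users, so the ratio is 1 − ln(1 − f)/(5λ). For f = 0.20 and λ = 0.05: 1 + 0.223/0.25 = 1.89. Cox estimates from simulation (45 per group) are slightly higher, because the added events all fall early.

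| Share f | Ratio by formula, λ = 10% / 5% | Cox HR, λ = 10% / 5% | False significance at 0.05 |
|---|---|---|---|
| 5% | 1.10 / 1.21 | about 1.1 / 1.2 | about 6–7% |
| 10% | 1.21 / 1.42 | about 1.2 / 1.5 | about 8–12% |
| 20% | 1.45 / 1.89 | about 1.5 / 2.0 | about 24–39% |
| 33% | 1.80 / 2.60 | about 1.9 / 2.7 | about 56–78% |

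A rarer background event makes it worse: at 2% per year and f = 10%, the formula gives 1 + 0.105/0.10 = 2.05. Counted from recruitment, the simulated hazard ratio is about 1.0. The simulation contains no other confounding, so this shows only that the change of time zero removes this mechanism.

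**Step 4. What is lost by counting from recruitment.** Expected progressions among 90 patients at the document's 2% per year:
- five years: 90 × (1 − 0.98^5) = 8.6
- two years: 90 × (1 − 0.98^2) = 3.6

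For an assumed hazard ratio of 0.5, power = Φ(√d/2 × |ln 0.5| − 1.96). With d = 9 events: Φ(1.040 − 1.96) = 18%. With d = 4: Φ(0.693 − 1.96) = 10%. The progression comparison is uninformative on either clock.

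**The case against.** The strongest reply is that no sentence says look-back events enter a Cox model. Table 1 is a schedule of data collection. A retrospective mark could mean history used to decide which arrhythmias are new, or serial ECG, echocardiographic and Holter data for the mixed models. A time origin is often left to a fuller document. This stands as a limit: the point is conditional. But the article itself counts the look-back as clinical follow-up and marks the two outcomes there, which favours the reading that they accrue in it.

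A reader might infer that all the event hazard ratios are biased. The documents do not support that. Table 1 restricts death, ICD implantation, transplantation and the composite to the prospective column, so the impossibility of dying in the look-back does no harm to the death outcome. The primary outcomes are measured at recruitment only and are untouched.

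A reader might also infer that every user who started in the window carries an event. That too goes beyond the text. The indication is any atrial or ventricular arrhythmia, while the outcome requires a sustained atrial arrhythmia or a ventricular tachyarrhythmia; a prompting arrhythmia such as extrasystoles need not qualify. Long-term users contribute no such event, and at a 5% share the effect is small.

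**Conclusion.** The concern holds for two secondary outcomes, cardiovascular events and CCC progression, on condition that look-back events are analysed as the five-year sentence implies. For cardiovascular events, the prompting arrhythmia biases the hazard ratio against AMIO. With no true effect it is about 1.1–1.2 at a 5% share, 1.2–1.5 at 10%, 1.5–2.0 at 20% and 1.9–2.7 at 33%, all under an assumed background rate of 5–10% per year. The documents give neither the share nor the rate, so no single figure can be claimed. For progression, selection on being alive and outside stage D at recruitment distorts the look-back in an uncertain direction.

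Table 1 is also inconsistent on this point. The composite is prospective only, yet it contains the two outcomes that are marked retrospectively. Their windows must be reconciled.

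**What to change.** 1. State that time zero for every Cox model is the patient's recruitment date and that only later events count.
2. Use the look-back as baseline history (prior arrhythmia, prior LVEF), both to define what is new and for adjustment. Relabel the retrospective cells for cardiovascular events and progression accordingly.
3. Restate follow-up for event outcomes as 2 years, and give the composite and its components the same window.
4. If look-back events are analysed as a supplement, treat AMIO as time-varying from its recorded start date, with earlier events and time assigned to unexposed time. Deleting the prompting arrhythmia there would remove events selectively from unexposed time and push the hazard ratio against AMIO. This analysis stays conditional on survival to recruitment.

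No change to the comparator or to recruitment is needed. Items 1–3 are changes of wording; item 4 needs AMIO start dates from records that are already being extracted. The real cost is events: expected progressions fall from about 8.6 to 3.6, so event comparisons should be presented as descriptive, and few adjustment covariates can be supported. Moving time zero does not remove confounding by indication after recruitment, which is why prior arrhythmia belongs among the baseline covariates.
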